#### Secondary outcomes

Secondary outcomes include:

• Quality of life (12-Item Short-Form Health Survey (SF-12) [46], Version 2). Data from the 12 items will be used to construct the physical and mental component summary scores. The SF-12 is a shorter questionnaire derived from the 36-Item Short-Form Health Survey (SF-36) and correlates well with the SF-36 (r > 0.94) [47].

• Priority for joint replacement surgery (Multi-attribute Arthritis Prioritisation Tool (MAPT) [48]). The MAPT is an 11-item questionnaire that assesses the need for joint replacement surgery. The questionnaire has high internal consistency (alpha = 0.85), test-retest reliability (ICC = 0.89) and correlation with the WOMAC (r = 0.78) [49].

• Participation in leisure time physical activity will be measured by the self-reported frequency and total duration over the past week of walking continuously, moderate physical activities and vigorous physical activities [50]. Participants will be categorised as participating in sufficient physical activity when more than 150 minutes of activity is accrued in at least five separate sessions per week [51].

• Fatigue ('how much of a problem has fatigue or tiredness been for you in the last week'). Responses will be marked on a 100-mm visual analogue scale, with anchor points being 'fatigue is no problem' and 'fatigue is a major problem' [52].

• Use of analgesics. The use of prescription and over-the-counter analgesics over the past week will be recorded, and the dosage adjusted for potency using defined daily dosage [53]

• Knee stability – the self-reported degree to which knee instability (partial giving way or full giving way) affects daily activities will be measured using the two stability items from the Activities of Daily Living Scale of the Knee Outcome Survey [54].

• Satisfaction with rehabilitation management ('how satisfied have you been with your rehabilitation programme since leaving the hospital where you had your surgery?') Responses will be required on a 6-point Likert scale, ranging from 'completely dissatisfied' to 'completely satisfied'.

• Walking speed (50-foot (15.24 m) timed walk [55]). Participants will be asked to walk as fast as possible within the limits of safety, with or without a walking aid.

• Knee range of motion. The centre of an extendable goniometer will be positioned over the lateral knee joint space with the arms aligned with the lateral midline of the femur using the greater trochanter as reference, and the lateral midline of the fibula using the head of fibula and lateral malleolus as reference [56]. Knee flexion will be measured as an active movement in sitting. Knee extension will be measured as an active-assisted movement in long sitting or supine with the heel supported the plinth during the movement.

• Lower limb power (stair climb test). Power on stair climb will be calculated using a formula that incorporates body mass, the time taken to ascend 10 stairs and total stair height [57]. This is a reliable and responsive measure in people with knee OA undergoing TKR [17].

• Maximal isometric knee flexion and extension strength. With the patient seated and the knee flexed at 90 degrees, a 'make test' will be performed against a handheld dynamometer, and the best of three attempts recorded. Strength will only be measured at the 6- and 12-month follow-up assessments because participants will be required to comfortably achieve 90 degrees of knee flexion.

The occurrence of adverse events will be sought from participants at each follow-up assessment. Adverse events will be defined as any musculoskeletal or cardiovascular event resulting in medical intervention or reduced function for three or more days. An independent Data Safety and Monitoring Committee (DSMC), comprising of experts in clinical trials, biostatistics and rehabilitation will be established to review data on adverse events after 300 study participants (half the planned study sample) have completed the six-month follow-up assessment. The DSMC will be charged with informing the study investigators if evidence emerges beyond reasonable doubt that treatment allocation is associated with an increased risk of serious adverse events that would be expected to change the practice of clinicians responsible for the rehabilitation of patients after primary TKR surgery.

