For the majority of patients, there are marked improvements after TKR in pain and physical function, with the maximum achievable benefit appearing around 6 months after surgery [20,21]. However, the magnitude of improvement is smaller than that demonstrated after total hip replacement surgery [21-23], and about 15% of patients still report moderate to severe pain a year after TKR despite no evidence of radiographic abnormalities [24]. Many years after TKR, patients are left with the lower limb muscle strength deficits evident prior to surgery [25-27] and with imbalances between knee extensor and flexor forces [25]. Poor ligamentous and neuromuscular control may result in destructive mechanical stresses and reduced control over anterior shear forces on the knee implant, potentially limiting implant longevity. It follows then, that muscle strengthening should be a major goal of rehabilitation. In support of this, achievement of greater knee extensor strength after TKR has been associated with improved physical function [26]. Younger people (<65 years of age) demonstrate less improvement after TKR [14] and have higher rates of revision surgery [10,28,29]. Effective rehabilitation may be particularly important in this younger group as they require prolonged implant longevity and are more likely to be in full-time employment or imposing greater physical demands on the knee implant.

In Australia, rehabilitation following TKR is mostly delivered in an outpatient setting by physiotherapists [30]. This rehabilitation commences immediately after discharge from the acute orthopaedic ward and is usually completed within 6 weeks, with resource-intensive one-on-one modes of delivery more common than class-based modes. However, evidence from randomised controlled trials suggests that such outpatient rehabilitation is no more effective than no treatment [31,32] or a home exercise programme [33,34]. One possible reason for the lack of demonstrable benefit is that the evaluated exercise programs did not specifically monitor or progress training intensity [31-34]. However training intensity is unlikely to be able to be progressed sufficiently to achieve meaningful changes in muscle strength in the first few weeks after TKR when patients are still experiencing the anaemia, pain and oedema inevitably associated with recovery from major orthopaedic surgery.

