### Interventions

#### Novel rehabilitation strategy

Stage 1: Initial home exercise programme (usually Week 1 to 6 after randomisation)

Participants will be provided with a written home exercise programme on discharge from acute care (Additional file 1). The exercises will focus on maintaining and improving active knee flexion and extension range of motion. Participants will repeat the exercises 5 to 10 times per exercise, three times daily. Participants' progress, including adherence to the home exercise programme, walking ability and knee symptoms (e.g. pain, wound healing, range of motion, swelling), will be monitored weekly by a research physiotherapist, with clinic visits in the first one or two weeks and by telephone calls thereafter.

Stage 2: Outpatient exercise classes (usually Week 6 to 14 after randomisation)

Approximately five weeks after randomisation, the research physiotherapist will commence screening during the weekly telephone calls to assess eligibility to commence the classes: (i) surgical wound healed, (ii) full weight-bearing tolerated on the operated limb, (iii) ambulating independently outdoors for more than 50 m, and (iv) not requiring daily opioid-based analgesics for knee pain. Participants will join the outpatient exercise classes as they become eligible.

The classes will be circuit-based and supervised by a physiotherapist. The one hour classes will be conducted twice a week. Participants will be encouraged to attend the ongoing classes for eight weeks. Each class will consist of a short warm up and cool down component, progressive functional and strengthening exercises, and a 20-minute monitored aerobic exercise session on a stationary bicycle (Additional file 1). In order to standardise this programme across centres, minimal equipment will be used and supervising physiotherapists will receive prior training from research staff as well as a written manual of procedures. Participants will record the loads, repetitions and sets for to each functional and strengthening exercise they complete, and the duration and exertion (maximal heart rate or the Borg Rating of Perceived Exertion Scale [36]) for the aerobic exercise, in an exercise diary during the classes.

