### Outcomes assessments

Assessments will be conducted at baseline (pre-admission clinic), and 6 weeks, 6 months and 12 months after randomisation by assessors blinded to treatment allocation. Demographic information collected at baseline will include height, weight, socioeconomic data (highest level of education completed, health insurance status, employment status, occupation), history of lower limb arthritis and joint surgery and the 19-item Hospital for Special Surgery Knee Replacement Expectations Survey [37,38]. This survey has been tested for internal consistency (Cronbach's alpha = 0.77) and test-retest reliability [37].

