### Statistical analysis

Statistical analysis will be by intention to treat and coded to ensure blinding to treatment allocation. For continuous data, two-way repeated measures ANOVA incorporating treatment groups at the three follow-up time points (6 weeks, 6 months and 12 months) will be carried out. The significance of any differences in dichotomous data (OMERACT-OARSI treatment responders, proportion of patients reporting sufficient leisure time physical activity, number of adverse events) will be tested using generalised estimating equations or linear mixed model. If there are chance imbalances in baseline patient characteristics hypothesised to influence the main outcomes, then statistical techniques that allow adjustment for confounding variables will be used as secondary analyses. If there are more than 5% missing data, sensitivity analysis allowing for different assumptions such as the best or worst possible scenario will also be reported for the main outcomes of the study.

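### Knee strength is tested at two follow-up visits but assigned to a three-visit model and, read literally, has no pre-operative value; the cost is precision and any account of change

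*Protocol article*

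**What the plan says.** The general schedule, under Outcomes assessments, has four occasions: "Assessments will be conducted at baseline (pre-admission clinic), and 6 weeks, 6 months and 12 months after randomisation". Under Secondary outcomes, strength alone is taken off it. The test position is fixed: "With the patient seated and the knee flexed at 90 degrees, a 'make test' will be performed against a handheld dynamometer". The visits are then restricted: "Strength will only be measured at the 6- and 12-month follow-up assessments because participants will be required to comfortably achieve 90 degrees".

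The Statistical analysis section gives one rule for continuous data: "two-way repeated measures ANOVA incorporating treatment groups at the three follow-up time points (6 weeks, 6 months and 12 months". Strength is not excepted. Baseline is neither a time point nor a routine covariate in that model. Adjustment is reserved for chance imbalance in baseline characteristics, where "statistical techniques that allow adjustment for confounding variables will be used as secondary analyses".

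The Background says that strength deficits present before surgery persist for years after it, and concludes that "muscle strengthening should be a major goal of rehabilitation".

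**The concern.** The visit schedule and the model do not fit together. The model needs a 6-week value that the schedule says will not exist.

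The second problem is the baseline. Taken at its word, the restriction to two visits also excludes the pre-admission clinic. Yet the reason given, comfortable flexion to 90 degrees, is mainly a difficulty of early recovery. It does not clearly apply before surgery, at a visit where the general schedule already has knee flexion, the timed walk and the stair climb measured.

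At stake is how well the trial can speak about a quantity central to its own rationale. Without a pre-operative value it cannot say how far strength changed or whether the earlier deficit resolved, and it cannot use a person's own starting strength to reduce noise. A later analysis plan can repair the model, but it cannot recover a baseline that was never measured.

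**Working it through.** **1. Schedule against model**

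| Visit | Strength measured (literal reading) | In the stated ANOVA |
|---|---|---|
| Baseline | no | no |
| 6 weeks | no | yes |
| 6 months | yes | yes |
| 12 months | yes | yes |

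The 6-week cell is empty in both arms, so the three-visit model cannot be estimated for strength. A group-by-time mixed model at 6 and 12 months, fitted to simulated data, could be estimated without difficulty.

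**2. Is the comparison valid without a baseline?**

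Yes. In a simulation of a follow-up-only comparison with no selective missing data (4000 replicates, no true effect), type I error was 0.050 and bias about 0. The issue is therefore precision and description.

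**3. The plan's own power figure**

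The Sample size section claims more than 90% power for clinically significant differences in each continuous secondary outcome. It gives no difference or SD for strength, so the claim cannot be reproduced. The steps below work in SD units.

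**4. Precision lost**

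Inputs from the article: 600 participants and 15% loss. Assumed: equal arms, two-sided 5% test, a single visit, no allowance for cross-over. The baseline to follow-up correlation r is also assumed.

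- Per arm: 600 × 0.85 / 2 = 255.
- Detectable difference at 90% power, unadjusted: (1.960 + 1.282) × √(2/255) = 0.287 SD.
- Standard error ratio with a baseline covariate: √(1 − r²).

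| r | SE ratio | Cut in SE | Cut in variance | Detectable at 90% power, adjusted | Unadjusted power at that difference |
|---|---|---|---|---|---|
| 0.3 | 0.954 | 5% | 9% | 0.274 SD | 87% |
| 0.5 | 0.866 | 13% | 25% | 0.249 SD | 80% |
| 0.7 | 0.714 | 29% | 49% | 0.205 SD | 64% |

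The same formula applies to a substitute covariate such as baseline stair-climb power, with r as its correlation with follow-up strength. That value may well be lower, so the 0.3 row shows what a weaker covariate would bring.

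**The case against.** **The schedule for strength is explicit and the model sentence is a summary.** A sensible analyst would model the visits collected. That is fair, and it makes the repair one clause long. But the article states both rules, and they conflict.

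**The word restricting the visits may apply to follow-up visits only,** so a baseline test may be intended. This is possible, since the general schedule includes baseline and the reason given explains skipping week 6. The missing baseline is the literal reading, not a certainty. In either case the sentence needs clarifying.

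**Lack of baseline adjustment is not special to strength.** This stands. The ANOVA uses baseline for no continuous outcome, so a reader who inferred that strength is the least precise physical measure would go beyond the document. The difference is that the other physical measures have a baseline value that could be used later. It also follows that a baseline test alone brings no gain in precision; the model must use it.

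**A reader might infer that stiff knees are excluded and that the analysis is therefore not by intention to treat.** The article does not support this. It states no exclusion, and an unobtainable test is missing outcome data, not a departure from analysis by allocated group. Nor does it establish a difference between arms. Of the home programme it says "The exercises will focus on maintaining and improving active knee flexion and extension range of motion", but it does not list the exercise content of usual care, and that stage usually ends by week 6, long before strength is tested. Under an invented scenario (10% untestable in control against 5% in the novel arm, strength and flexion correlated at 0.4), simulated bias was about −0.03 SD and type I error 0.06. That is small, rests wholly on assumptions, and runs against the novel arm.

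**Conclusion.** The point holds in a limited form. The stated model cannot be run for strength, and as written there is no pre-operative strength value, for a reason that does not clearly cover the pre-admission visit. The randomised comparison at 6 and 12 months is valid without one. The losses are the ability to describe change and, if r is 0.5 to 0.7, a standard error that adjustment would have made 13% to 29% smaller. Those correlations are assumptions.

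Strength is one of many secondary outcomes. The WOMAC, responder and economic analyses are untouched. The point is still worth acting on because the repair is cheap and a baseline value cannot be obtained once the participant has had surgery.

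**What to change.** 1. In Statistical analysis, state that strength is modelled at 6 and 12 months only, adjusted for baseline stair-climb power, which the general schedule already collects. This costs wording only. The gain depends on how well stair-climb power correlates with strength and may fall below the 13% to 29% range.

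2. Preferably, add the same handheld dynamometer test at the pre-admission visit for participants who can comfortably reach 90 degrees, and use it as the covariate instead. The cost is a few minutes at an existing visit with a device the trial already uses, plus some missing baseline values, for which the analysis needs a stated rule. If baseline testing is already intended, say so under Secondary outcomes.

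3. Optionally, report by arm how many participants could not reach the test position at 6 and 12 months. This costs one recorded item per visit.

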### Health economic outcomes

Participants will prospectively record in a patient diary the following:

• presenteeism (self-reported capacity to work or perform daily activities) [58-60]

• instances of absenteeism

• use of healthcare and community services

• out-of-pocket costs of community services

These data will be collected over three six-week time periods from: (i) discharge from acute care, (ii) the 6-week follow-up assessment, and (iii) the 6-month (26-week) follow-up assessment.

Presenteeism will be rated from 0% (unable to do usual work/activities) to 100% (fully functioning). Absenteeism is defined as days off work (including home, volunteer or carer duties) due to TKR. The use of healthcare (e.g. visits to medical practitioners, physiotherapists, hospitalisation) and community (e.g. meals on wheels) services will be recorded in terms of the type of service, date of use and number of hours/days. Costs of community services will be the out of pocket costs incurred by participants. The use of medication will be included as a health economic outcome and will be collected at the time of each follow-up assessment.

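### Adverse events during the week 6–14 classes are first formally asked about 12 to 20 weeks later, and the number of events, a count, is listed as dichotomous data

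*Protocol article*

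**What the plan says.** **When events are asked about.** The paragraph on adverse events that closes the Secondary outcomes section states: "The occurrence of adverse events will be sought from participants at each follow-up assessment". The Outcomes assessments section sets the follow-up times: "6 weeks, 6 months and 12 months after randomisation by assessors blinded to treatment allocation". The Health economic outcomes section equates six months with 26 weeks ("the 6-month (26-week) follow-up assessment").

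**What counts as an event.** The definition is "any musculoskeletal or cardiovascular event resulting in medical intervention or reduced function for three or more days".

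**When the classes run.** The Interventions section gives "Stage 2: Outpatient exercise classes (usually Week 6 to 14 after randomisation", twice weekly for eight weeks. Start dates vary: "Participants will join the outpatient exercise classes as they become eligible".

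**How events are analysed.** The Statistical analysis section, in its list of dichotomous data, has "sufficient leisure time physical activity, number of adverse events) will be tested using generalised estimating equations or linear mixed model".

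**What else is recorded.** Both arms keep a patient diary over three six-week periods, the second starting at the 6-week assessment. It records healthcare use with type of service and date, days off work or usual duties, and self-rated capacity for daily activities. The article presents it as a health economic instrument and does not name it as a source of adverse events. In the novel arm only, knee pain, range of motion and swelling are checked at each class, to guide exercise progression.

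**The concern.** The classes are what the novel strategy adds, so a harm comparison should be able to see events that happen in them. On the stated schedule they fall wholly between the 6-week and 6-month enquiries, and the participant has to remember them at week 26. Part of the definition is reduced function for as little as three days, and such an event could be forgotten over several months.

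The analysis wording adds a second difficulty. A number of events is not dichotomous. The text can mean any/none per participant or per window, or it can mean a count, and these call for different models. A linear mixed model is the natural choice for neither. Under the any/none reading, a participant with three events in a window contributes the same as a participant with one.

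At stake is whether the safety comparison gives a usable event rate for the period in which the two strategies differ most in exercise intensity.

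**Working it through.** **1. Lag from event to first enquiry.** Inputs: six-month visit at week 26 (Health economic outcomes); classes usually weeks 6 to 14 (Interventions). Lag = 26 − week of event.

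- First class week: 26 − 6 = 20 weeks.
- Last class week: 26 − 14 = 12 weeks.

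For a participant who starts at week *s* and attends for eight weeks, the range is 26 − (*s* + 8) to 26 − *s*, so later starters have a shorter lag. Screening begins at about week 5, so someone who starts before the 6-week visit could be asked about the first classes at that visit.

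**2. Cover from the existing diary.** The second period starts at the 6-week assessment and lasts six weeks: 6 + 6 = week 12. Classes usually end at week 14, so 14 − 12 = 2 weeks of the usual class period have no prospective record in both arms. Between week 12 and the week 26 visit the gap is 26 − 12 = 14 weeks.

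**3. Cost of reading the count as any/none.** The article gives no adverse event rate, so a range is assumed, with Poisson events at mean *L* per participant per visit window. Share of events lost = 1 − (1 − e^(−L))/L. For *L* = 0.5: (1 − 0.607)/0.5 = 0.787, so 21.3% is lost.

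The table assumes a true rate ratio of 1.5. Power assumes two-sided 0.05 and 255 per arm (300 × 0.85, using the article's 15% loss to follow-up).

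| Control rate per window (assumed) | Control events lost | Novel-arm events lost | Ratio seen as any/none | Power, any/none | Power, count |
|---|---|---|---|---|---|
| 0.05 | 2.5% | 3.7% | 1.48 | 20% | 20% |
| 0.1 | 4.8% | 7.1% | 1.46 | 34% | 35% |
| 0.2 | 9.4% | 13.6% | 1.43 | 57% | 61% |
| 0.3 | 13.6% | 19.5% | 1.40 | 71% | 78% |
| 0.5 | 21.3% | 29.6% | 1.34 | 86% | 94% |

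For a true doubling, the any/none ratio is 1.95 at a control rate of 0.05 and 1.61 at 0.5. The loss is small when events are rare and material only when repeats within a window are common.

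**4. Stated figure.** The article gives no recall interval, event rate or safety power, so there is no figure of its own to reproduce on this point.

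**The case against.** The best defence is that an article condenses a fuller protocol. Event forms and source documents may be described there, and link function and distribution belong in an analysis plan. The formal enquiry follows the same schedule in both arms, with blinded assessors. The diary already captures dated medical visits and hospital stays for about weeks 6 to 12, which overlaps the medical-intervention part of the definition. Generalised estimating equations can handle counts as well as binary data, and with one response per visit they keep repeats that fall in different windows.

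Much of this stands and limits the point. It does not remove two things the article itself fixes: an enquiry tied to three visits, and a count labelled dichotomous.

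A reader might infer more than the documents support:

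- *That short events drop out because the outcome is dichotomised.* They do not. Events under three days without medical intervention are excluded by the definition, equally in both arms. Brief qualifying events may be forgotten, but nothing in the article measures this.
- *That the classes are the highest-risk period and get the longest delay.* The article does not say so. It describes the first weeks as those of anaemia, pain and oedema, and sets recovery criteria for joining classes. The longest window is the one between 6 and 12 months (52 − 26 = 26 weeks).
- *That recall differs between arms.* Novel-arm participants have checks at each class, but usual care is typically individual physiotherapy, which may also involve knee review. A difference is possible in either direction and is not shown.
- *That the safety committee is left without a sound basis.* Its stated remit is serious adverse events, which forgotten or repeated minor events barely touch.

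**Conclusion.** The point holds in a limited form. On the usual schedule, class-period events are first formally asked about 12 to 20 weeks after they occur. Under-recall of brief qualifying events is plausible, but its size and direction between arms cannot be derived from the article.

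Separately, the Statistical analysis section contradicts itself by listing a count as dichotomous. If this is resolved as any/none, the loss is confined to repeats within a visit window: about 2.5% to 21% of control-arm events over assumed rates of 0.05 to 0.5 per window, with Poisson events. At the low end the effect on power is negligible; at the high end it is 86% against 94% for a true rate ratio of 1.5.

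This is a worthwhile, inexpensive improvement to the harm comparison. It does not bear on the primary efficacy comparison.

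**What to change.** **Capture.**
- Add one dated adverse event item, using the article's own definition and identical wording in both arms, to the patient diary.
- Extend the second diary period in both arms from about week 12 to at least week 14, the usual end of classes. Allow a further margin, equal in both arms, for participants who start classes late.
- Name the diary item and the visit question together as the adverse event source. Class records alone should not generate events for the between-arm comparison, because they exist in one arm only.

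**Analysis.** In the Statistical analysis section, separate two outcomes:
- the proportion with at least one event, by a binary model (for example generalised estimating equations with a logit link);
- the number of events, by a Poisson or negative binomial model with time at risk.

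Remove the linear mixed model as an option for these data. Tabulating events by visit window (0–6 weeks, 6 weeks–6 months, 6–12 months) would show the class period's window on its own.

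**Cost.** One diary item, about two more diary weeks (longer if the margin for late starters requires it), slightly more participant burden and a little more analysis. No change to visits, sample size or treatment.
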